## Abstract

**Introduction:**

The aim of the cervical ripening at home or in-hospital—prospective cohort study and process evaluation (CHOICE) study is to compare home versus in-hospital cervical ripening to determine whether home cervical ripening is safe (for the primary outcome of neonatal unit (NNU) admission), acceptable to women and cost-effective from the perspective of both women and the National Health Service (NHS).

**Methods and analysis:**

We will perform a prospective multicentre observational cohort study with an internal pilot phase. We will obtain data from electronic health records from at least 14 maternity units offering only in-hospital cervical ripening and 12 offering dinoprostone home cervical ripening. We will also conduct a cost-effectiveness analysis and a mixed methods study to evaluate processes and women/partner experiences. Our primary sample size is 8533 women with singleton pregnancies undergoing induction of labour (IOL) at 39+0 weeks’ gestation or more. To achieve this and contextualise our findings, we will collect data relating to a cohort of approximately 41 000 women undergoing IOL after 37 weeks. We will use mixed effects logistic regression for the non-inferiority comparison of NNU admission and propensity score matched adjustment to control for treatment indication bias. The economic analysis will be undertaken from the perspective of the NHS and Personal Social Services (PSS) and the pregnant woman. It will include a within-study cost-effectiveness analysis and a lifetime cost–utility analysis to account for any long-term impacts of the cervical ripening strategies. Outcomes will be reported as incremental cost per NNU admission avoided and incremental cost per quality adjusted life year gained.

**Research ethics approval and dissemination:**

CHOICE has been funded and approved by the National Institute of Healthcare Research Health Technology and Assessment, and the results will be disseminated via publication in peer-reviewed journals.

**Trial registration number:**

ISRCTN32652461.

Strengths and limitations of this studyThis is a large study to evaluate the safety of at-home cervical ripening.We will set up a platform for data collection using electronic health records to enable future research into rare safety outcomes.The study includes assessment of women’s views and experiences using validated questionnaires as well as qualitative methods.Observational design of the study makes it vulnerable to residual confounding.

## Introduction

Induction of labour (IOL) is the most common obstetric intervention offered to women when risks of continuing the pregnancy are thought to outweigh risks of birth. Increases in IOL rates over the past 10 years mean that now 29.6% of all pregnant women in the UK have their labour induced.^1^ IOL at term, when compared with expectant management of pregnancy, reduces caesarean birth, maternal hypertensive disease and complications,^2^ as well as being associated with a reduction in perinatal mortality.^3 4^ The demands on maternity services are increasing to accommodate increasing rates of IOL.^5^ Although IOL (compared with expectant management) reduces overall hospital stay, it increases the time on labour and delivery wards,^2^ having a major impact on resources, staffing and negatively impacts on women’s experience of labour.^6–8^

Cervical ripening is a key component of IOL.^9^ It may initiate labour, but is often followed by artificial rupture of membranes±intravenous oxytocin infusion. National Institute for Health and Care Excellence (NICE) guidance^10^ recommends pre-induction cervical ripening in all women having IOL unless there is a contraindication.

Traditionally, cervical ripening has been performed entirely in-hospital, to allow monitoring of maternal/fetal well-being and early recognition of complications.^11^ However, an increasing number of UK maternity units offers outpatient (home) cervical ripening. As the rate of IOL is increasing, home cervical ripening may provide opportunities to reduce the burden on the NHS, for example, by reducing hospital stay during IOL. However, the safety and acceptability of home cervical ripening have not been fully evaluated. NICE^10^ identified the need to assess the safety, efficacy and clinical and cost-effectiveness of outpatient and inpatient IOL in the UK setting, taking into account women’s views. A recent Cochrane review found insufficient evidence to draw conclusions on the efficacy, safety and cost-effectiveness of home IOL and indicated that large prospective cohort studies would be needed.^12^ Maternity service users have identified IOL as an important research topic,^13^ and women have reported specific negative experiences such as increased pain and anxiety and lack of support which may be alleviated by home cervical ripening.^8^ Potential NHS cost savings of home cervical ripening could be offset by increased costs of any additional morbidity resulting from home cervical ripening, costs to parents may be increased and acceptability of home cervical ripening is unknown. Health services need to balance the full resource impact of IOL with the need to provide safe and acceptable care.

In the cervical ripening at home or in-hospital—prospective cohort study and process evaluation (CHOICE) study, we will perform an observational cohort study with a cost-effectiveness analysis and process evaluation to address the question, ‘Is it safe, effective, cost-effective and acceptable to women to carry out home cervical ripening during IOL?’. These analyses will provide information to help women and their caregivers make informed decisions around how to have IOL.

Our main aim is to compare the setting of cervical ripening at home versus in-hospital. As the NICE recommended agent for cervical ripening is vaginal prostaglandin, our primary comparison will be home dinoprostone versus in-hospital dinoprostone. In order to future-proof the study, we will include a secondary comparison: home cervical ripening with balloon catheter versus home cervical ripening with dinoprostone. By including two different methods of home cervical ripening within our study, we will provide initial comparative evidence on these two methods of home labour induction.

## Methods and analysis

### CHOICE: a prospective cohort study

#### Study design and setting

We will carry out a prospective multicentre cohort study using de-identified clinical data from electronic hospital records. The primary outcome will be non-inferiority of a neonatal unit (NNU)/special care admission for 48 hours or longer, initiated within 48 hours of birth.

The study will be performed in at least 26 UK obstetric units, 14 of which offer exclusively in-hospital cervical ripening and 12 offer dinoprostone cervical ripening both in-hospital and at home.

Participating maternity units will be purposively selected to represent the diverse range of maternity service settings in the UK, and include urban tertiary referral units, mid-sized urban district general hospitals and small, more isolated, rural units.

#### Data sources

Data will be collected directly from electronic maternity (and neonatal) records for participants who had babies admitted to an NNU. These data are recorded by clinical staff (midwives, doctors and neonatal nurses) during the course of antenatal, intrapartum and postpartum care. Existing data fields, supplemented by new bespoke, data entry fields enabled in the maternity dataset at participating sites will be used. Unless women opt out of secondary data use (from similar studies, we estimate <1% will opt out), de-identified data will be transferred from participating sites to a secure University of Edinburgh server for analysis.

No personal data will be collected. Potentially identifiable data, such as the date and time of birth, date of events such as commencing cervical ripening and hospital discharge, will be converted into gestation at birth (weeks+days); and antenatal and postnatal events into ‘t–x’ and ‘t+x’ hours and days, respectively.

#### Population, inclusion and exclusion criteria

We will initially apply broad inclusion criteria and collect data from all women having IOL at 37+0 weeks’ gestation or more to create a cohort for analyses. Women who have opted out of data provision will be excluded.

We will then apply more stringent inclusion and exclusion criteria at the analysis stage for a suite of nested analyses. In our primary analysis, we will create a cohort of women with ‘uncomplicated’ (ie, those with no identified risk factors for adverse maternal or perinatal outcomes defined below) pregnancies in whom there was no contraindication to home cervical ripening, who had singleton pregnancies with IOL at 39 weeks’ gestation or more. This group will include women having IOL for post-dates, but also women having IOL because of maternal or clinician preference, IOL for maternal age and IOL for discomfort or social indications. Exclusion criteria will consist of grand multiparity (six or more previous births), previous caesarean section, antepartum stillbirth (before cervical ripening initiated), class III obesity at booking (body mass index (BMI): 40 kg/m^2^ or more), prelabour rupture of membranes (ROM) documented as primary or other indication for IOL (prolonged ROM, spontaneous ROM and suspected spontaneous ROM), maternal or fetal condition that would or could preclude home cervical ripening documented as primary or other indication for IOL (maternal conditions: proteinuria; hypertension; antepartum haemorrhage; diabetes; obstetric cholestasis; obstetric history; pre-eclampsia; pregnancy induced hypertension (PIH)/pre-eclampsia (PET) (not defined); PIH; PET; thrombophilia; fetal conditions: oligohydramnios; reduced liquor volume; macrosomia; intrauterine growth restriction; static growth; congenital fetal anomaly; polyhydramnios; abnormal cardiotocograph (CTG)/Doppler; breech; reduced fetal movements and termination of pregnancy for fetal anomaly).

We will explore the potential for additional analyses, which may include IOL for other indications (eg, reduced fetal movements) or in other populations (eg, multiple pregnancies and women with a previous caesarean birth). However, in general, home cervical ripening is only offered to ‘low risk’ women, so we anticipate that numbers of higher risk women having home IOL may not be high enough for meaningful analyses.

#### Exposure and outcomes

Our primary aim is to compare home versus in-hospital cervical ripening. We will collect data at individual level. The exposure group will be women who, at the start of the cervical ripening process, plan to have home cervical ripening. The comparator group will be women who planned to have in-hospital cervical ripening from maternity units not offering home cervical ripening. This will minimise potential bias arising from the fact that, in maternity units which offer both home and in-hospital cervical ripening, the risk of complications in the babies of women having home cervical ripening (lower risk pregnancies) is inherently different to that of babies of women having in-hospital cervical ripening (higher risk pregnancies).

As the NICE recommended agent for cervical ripening is vaginal prostaglandin, our primary comparison will be home dinoprostone versus in-hospital dinoprostone. Dinoprostone is now most commonly administered as 10-mg slow-release pessary (Propess, Ferring), which stays in place for 24 hours. We will use this formulation in our primary comparison.

We will include a secondary exploratory comparison—home cervical ripening with balloon catheter (exposure) versus home cervical ripening with dinoprostone (comparator), to explore if there are any indications of different safety profiles of these two methods of home cervical ripening.

Our proposed primary outcome will be admission to an NNU/special care baby unit for 48 hours or longer, initiated within 48 hours of birth. NNU admission is a marker of neonatal morbidity and is the leading core outcome defined for studies of IOL.^14^ Any increase in NNU admission of term babies is undesirable due to the separation of mother and baby. However, NNU admission rates are highly variable between maternity units and are likely to depend on local policies and culture. We, therefore, plan to use a primary outcome, which represents more severe neonatal morbidity (admission to a NNU within 48 hours of birth for 48 hours or longer), which is less likely to be influenced by site-specific factors. We may re-define the parameters of NNU admission used in the primary outcome after analysis of pilot data (see section ‘Pilot phase’).

We have prespecified a number of secondary outcomes to assess the safety of home cervical ripening with respect to neonatal and maternal morbidity, listed in table 1. These include outcomes from a core outcome set for studies of IOL.^14^ We will also include secondary outcomes relating to the effectiveness of home cervical ripening and to explore whether the setting of cervical ripening influences subsequent labour and birth. Mother and baby outcomes were suggested by our lay consultation as important to include. We will use birth weight, birth weight centile, small for gestational age and large for gestational age as parameters to check the validity of our matching procedures in analyses. Birth weight is an objective outcome that may represent pregnancy complications, but extremely unlikely to be affected by the setting of cervical ripening. Comparison of birth weights between groups should provide reassurance that we have minimised systemic bias in our analyses.

**Table 1 T1:** Secondary outcomes

Safety outcomes	**Baby** Any neonatal unit (NNU) admission (any level of care) Neonatal intensive care unit (NICU) admission Duration of NNU stay Duration of NICU stay Apgarscore <7 at 5 min Apgar score <4 at 5 min Arterial cord blood pH <7.1 Arterial cord base excess >12 mmol/L Neonatal seizures Hypoxic ischaemic encephalopathy (as recorded by care givers) Level 2 or level 3 hypoxic ischaemic encephalopathy (as recorded by care givers) Meconium aspiration syndrome Mechanical ventilation Intracranial haemorrhage Stillbirth after admission/first attendance for induction of labour (excluding deaths from congenital anomalies) Early neonatal death up to 7 days after birth (day 0–6; excluding deaths from congenital anomalies) Treatment for neonatal sepsis (defined as positive blood, cerebral spinal fluid, or urine culture or cardiovascular collapse or X-ray confirming infection) (exploratory outcome) Treatment in NNU for neonatal infection (defined as antibiotic treatment and temperature ≥37.5°C or <35.5°C) (exploratory outcome) Treatment for neonatal jaundice (defined as peak total bilirubin of at least 15 mg or the use of phototherapy) (exploratory outcome)	**Maternal** Intensive care unit transfer High dependency level care Hyperstimulation or tachysystole (as defined by care givers) Hyperstimulation or tachysystole causing cardiotocograph (CTG) abnormality (as defined by care givers) Umbilical cord prolapse Birth outwith hospital Postpartum haemorrhage 1000 mL or more Maternal fever 38°C or more after commencing cervical ripening (exploratory outcome)
Effectiveness outcomes	Time from first cervical ripening agent to admission to labour ward/birth unit Time from first cervical ripening agent to birth More than one cervical ripening agent used Duration of antenatal hospital stay for cervical ripening Duration of labour ward admission until birth Duration postnatal hospital stay (mother) Total hospital stay Hours spent at home Oxytocin use Mode of birth Birth in obstetric unit Birth in alongside midwifery unit (if available at that site)	
Mother baby outcomes	Breastfeeding at discharge from maternity care Skin to skin at birth	
Cost effectiveness	**Primary health economic outcomes** Incremental cost per neonatal admissions avoided (home vs in-hospital) Incremental quality adjusted life year (QALYs) (home vs in-hospital) **Other (exploratory) economic outcomes** Incremental cost per hour prevented from hospital admission to delivery/birth Incremental cost per neonatal admission avoided (home balloon catheter vs home dinoprostone) Incremental cost per QALY (home balloon catheter vs home dinoprostone) Incremental cost per hour prevented from hospital admission to delivery/birth (home balloon catheter vs home dinoprostone)	
Outcomes to check comparability of groups/matching	Birth weight Birth weight centile Small for gestational age (<10th centile for gestational age) Large for gestational age (>90th centile for gestational age)	
Qualitative CHOICE process evaluation outcomes	**Primary qualitative outcome** Sense of control (agentry) in labour **Secondary qualitative outcomes** Women’s satisfaction with induction of labour care Women’s postnatal psychological well-being Women’s overall evaluation of their labour and birth experience (qualitative analysis) Costs incurred by the woman and family	

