Establishing the appropriate non-inferiority margin was complicated by recognition that the dimensions that are hypothesised to show benefit, that is, acceptability to women and partners, and a reduction in costs appeal to different audiences—women will be primarily interested in acceptability and largely indifferent to costs (in a free at point of care NHS), whereas the potential reduction in costs will likely be the primary focus for the healthcare provider. We were also conscious that due to the inflation of the sample size due to (a) clustering, (b) losses due to non-matching in the propensity analysis and (c) loss to follow-up, the sample size for a smaller non-inferiority margin would quickly become not feasible within a realistic budget and timeframe. Given that, regardless of a superiority or non-inferiority design, any specific sample size will estimate the treatment effect to a certain level of precision (eg, the width of a 95% CI), we are confident that our final comparison group of 1920 in each arm (with ~115 NNU admissions in each arm (see sample size calculation below)), we will generate sufficient high-quality evidence to definitively answer the questions around safety, effectiveness, acceptability and cost-effectiveness for this important question

For the principal analysis of the primary outcome, we will use mixed effects logistic regression for the non-inferiority comparison of NNU admission within 48 hours of birth for 48 hours or longer (Yes/No). As sensitivity analyses to demonstrate that the estimated treatment effects are robust to the chosen method, we will also explore propensity score weighting (by inverse probability of receiving specified treatment) and single-stage regression, without using any propensity scoring, adjusting directly for the baseline factors relevant for treatment indication. We will also use propensity score matched (PSM) adjustment to control for treatment indication bias. The logistic model underlying the PSM will include variables such as age, Bishop’s score, previous vaginal birth, c-morbidities and relevant hospital-level factors, with 1:1 matching. Potential confounding variables will be identified before the start of the analysis, and these will be finalised after exploration of the data at the pilot stage, through the creation of directed acyclical graphs.

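### As worded, the primary outcome scores a stillbirth after ripening starts, or a death before 48 hours in the neonatal unit, as a non-event; the definition should state a rule for death

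*Protocol article*

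**What the plan says.** The event is set out in the protocol article under Exposure and outcomes: "Our proposed primary outcome will be admission to an NNU/special care baby unit for 48 hours or longer, initiated within 48 hours of birth". The same section explains that the 48-hour version was chosen as a "primary outcome, which represents more severe neonatal morbidity (admission to a NNU within 48 hours of birth for 48 hours or longer" and as less sensitive to local admission policy. Under Statistical analysis it is the dependent variable of the principal model, a "non-inferiority comparison of NNU admission within 48 hours of birth for 48 hours or longer (Yes/No". Study design and setting and the health economic section repeat the definition. None of these places mentions death.

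Among the exclusions for the primary cohort, the only one that concerns the baby's death is "antepartum stillbirth (before cervical ripening initiated".

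Death appears in Table 1 as two secondary safety outcomes: "Stillbirth after admission/first attendance for induction of labour (excluding deaths from congenital anomalies" and "Early neonatal death up to 7 days after birth (day 0–6; excluding deaths from congenital anomalies". Table 1 also lists "Any neonatal unit (NNU) admission (any level of care".

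One of the two primary health economic outcomes in Table 1 is "Incremental cost per neonatal admissions avoided (home vs in-hospital"; the other is incremental QALYs.

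Under Pilot phase, the NNU admission parameters may be redefined. The criteria given are the intraclass correlation (ICC) and the severity of the outcome; death is not among them.

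**The concern.** The duration condition is meant to move the outcome towards more serious illness. Read literally, it drops the most serious cases: a baby who dies in the NNU at 10 hours counts under any NNU admission but not under the primary outcome. If a change of setting turned some long stays into deaths, the primary outcome would improve.

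The non-inferiority conclusion rests on this outcome alone. The secondary death outcomes have no stated margin, are not adjusted for multiplicity, carry a caveat about type 1 error, and will probably contain very few events. The ratio of cost per admission avoided has the same weakness, because a death before 48 hours enters it as an admission that did not happen.

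**Working it through.** **Step 1. How each course is scored under the present wording.**

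| Course | In primary cohort? | Primary outcome | Where it appears in Table 1 |
|---|---|---|---|
| Stillborn before ripening | No (excluded) | none | none |
| Stillborn after ripening starts | Yes | No | Stillbirth |
| Live born, dies before NNU admission | Yes | No | Early neonatal death |
| Admitted, dies in NNU before 48 h | Yes | No | Early neonatal death; any NNU admission |
| Well, never admitted | Yes | No | none |
| Admitted within 48 h, stays 48 h or longer | Yes | Yes | Any NNU admission |

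Rows two to four score the same as row five. Table 1 leaves out deaths from congenital anomalies in both death outcomes.

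**Step 2. Reproduce the plan's sample size.** Inputs from the Sample size section: 6% in both arms, 4-point margin, one-sided alpha 2.5%, power 90%, ICC 0.01, 12 clusters of 160 per arm.

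- n per arm without clustering = (1.960 + 1.282)² × 2 × 0.06 × 0.94 / 0.04² = 741
- Design effect = 1 + 159 × 0.01 = 2.59
- 741 × 2.59 = 1919, against 1920 stated
- 1920 × 2 / 0.5 / 0.9 = 8533, as stated
- 1920 × 0.06 = 115 events per arm, as stated

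The effective size per arm is 1920 / 2.59 = 741.3. The standard error of the risk difference is √(2 × 0.06 × 0.94 / 741.3) = 0.0123, so the 95% CI half-width is about 2.4 points and power is 90.0%.

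**Step 3. Count these deaths as events, with equal risk in both arms.** The documents give no death rate, so the rates here and in Step 4 are assumptions. The same amount is added to both arms, so the risk difference does not change. Replacing 0.06 by 0.06 + d in Step 2 gives:

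| Assumed deaths per 1000 | Deaths per arm (1920 × d) | n per arm for 90% power | Power at 1920 |
|---|---|---|---|
| 0.5 | 1.0 | 1935 | 89.8% |
| 1 | 1.9 | 1950 | 89.6% |
| 2 | 3.8 | 1979 | 89.1% |
| 5 | 9.6 | 2069 | 87.8% |

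**Step 4. Unequal risk.** The present wording understates the composite risk difference by δ = home rate minus hospital rate. Suppose the true composite difference sits exactly on the 4-point margin. The chance of declaring non-inferiority, which should be 2.5%, is then Φ(δ/SE − 1.96), with SE = √([0.06 × 0.94 + p(1 − p)] / 741.3) and p = 0.10 − δ.

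| Deaths per 1000, home v hospital | Shift in risk difference (points) | Share of the 4-point margin | Chance of declaring non-inferiority |
|---|---|---|---|
| 1 v 0.5 | 0.05 | 1.25% | 2.7% |
| 2 v 1 | 0.1 | 2.5% | 2.9% |
| 3 v 1 | 0.2 | 5% | 3.5% |
| 5 v 1 | 0.4 | 10% | 4.7% |
| 1 v 2 | −0.1 (against home) | −2.5% | 2.1% |

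**Step 5. Scale.** One baby is 1/1920 = 0.05 points. Five excess home deaths are 5/1920 = 0.26 points. A shift of one point needs 0.01 × 1920 = about 19 excess deaths.

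Steps 2 to 5 use the normal approximation on the risk difference, not the planned mixed logistic model.

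**The case against.** **No passage says these babies score No.** True: this follows from the wording. A separate statistical analysis plan is announced and might settle the coding and the denominator. But the event definition is stated in this article several times without a death component, so adding death later would change the stated outcome rather than fill in detail. The pilot clause does not reach the problem either.

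**A reader might infer that the endpoint is biased towards finding home ripening safe, with all the error running one way.** The documents do not support that. Unclassified deaths occur in both arms and cancel on the risk difference if equally frequent; with more in hospital the shift goes against home. The protocol does argue that home ripening cannot plausibly be expected to be safer, and says hospital ripening exists for monitoring and early recognition of complications. That makes an excess at home the direction to worry about, but it is a premise, not data.

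**The effect is small and the cohort is low risk.** This stands. The primary cohort is restricted to uncomplicated singleton pregnancies, and five excess deaths added to about 115 expected events would rarely change the verdict. The composite would not make the study able to detect excess mortality; that still depends on seeing deaths separately, which Table 1 provides and for which the plan allows exact methods.

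**The chosen outcome is defensible.** Also fair: the article calls NNU admission the leading core outcome for induction studies and gives a reason for the 48-hour version. Stating how death is handled does not give up that choice.

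**Economics.** It would be wrong to infer that the whole evaluation rewards death. QALYs are a primary economic outcome too, and a lifetime cost-utility analysis is planned. The weakness is confined to the cost-per-admission ratio.

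**Conclusion.** The concern holds in limited form. By its wording, the primary safety outcome puts a stillbirth after ripening starts, a death before admission and a death in the NNU before 48 hours in the same category as a healthy baby. This is a fault in the definition, not just missing detail.

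Any effect on the non-inferiority result is conditional and probably small: none on the risk difference at equal death rates, 0.05 to 0.4 points in favour of home for assumed excesses of 0.5 to 4 per 1000 at home (about 1 to 8 babies, 1920 × 0.0005 to 1920 × 0.004), and the reverse if deaths are more frequent in hospital. These sizes rest entirely on assumed rates. It should be fixed because the fix is cheap and a safety endpoint should not improve when a long stay becomes a death; the likely numerical effect does not make it critical.

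**What to change.** Redefine the primary event as any of:

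- NNU admission of 48 hours or longer starting within 48 hours of birth;
- stillbirth after cervical ripening starts;
- neonatal death before the 48-hour criterion could be met.

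Apply the congenital-anomaly exclusion of Table 1 to both death components, and report all components separately by arm. If the sponsor prefers to keep the present outcome, state how these deaths are coded and prespecify the composite as a key sensitivity analysis. Either way, use the same event in the cost-per-admission-avoided ratio.

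The cost is a sentence or two. Table 1 already lists the outcomes needed, and the latest time at which a baby could still be completing a qualifying stay is 48 + 48 = 96 hours after birth, inside its day 0–6 window. The drawback is that the endpoint becomes a composite of unlike components. At assumed death rates of 0.5 to 2 per 1000 in both arms, power at 1920 per arm is 89.8 to 89.1%; restoring 90% would take 1935 to 1979 per arm.

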Similar analyses will be used for analyses of secondary outcomes, using logistic, linear, negative binomial and time-to-event regressions. For example, we will analyse the duration of hospital stay during IOL, time spent at home, total hospital stay and time to birth using linear models; while birth outwith hospital and breastfeeding will be analysed using logistic regression; and mode of birth using multinomial logistic regression.

For the remaining maternal secondary outcomes, we will include hyperstimulation, ≥1 induction agent, oxytocin use for induction or augmentation, maternal ICU/High dependency unit admission, haemorrhage, uterine rupture, pulmonary embolus and cardiorespiratory arrest. For the neonatal secondary outcomes, we will include meconium aspiration syndrome, respiratory support, neonatal infection, umbilical cord prolapse, neonatal birth trauma, neonatal encephalopathy (Grade II/III), therapeutic hypothermia and neonatal death. Logistic regression and Poisson or negative binomial regression, possibly inflated for excess zeros will be used as appropriate. For outcomes with a small number of events, we will use the appropriate exact regression procedure. As per the primary outcome, we will assess the influence of missing data for secondary outcomes using appropriate sensitivity-type analyses. We recognise that there are many secondary outcomes being analysed, as per the recommended core outcome set.^17^ We do not propose to make any formal statistical adjustment for the multiple comparisons. However, a caveat will be clearly expressed regarding the possibility of type 1 statistical error, given the multiple comparisons made. We will consider the following subgroup analyses, based on sufficient numbers to allow meaningful analyses: (a) nulliparous and parous women; (b) indication for IOL (post-dates IOL; maternal or clinician preference; maternal age and discomfort or social indication).

We propose the following sensitivity analyses: (a) within-site comparison of home versus in-hospital cervical ripening (restricted to sites that offer home cervical ripening), (b) per protocol analysis (women who actually are discharged home after commencing cervical ripening) and (c) complete case analysis to assess the effect of any strategies to deal with missing data.

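### The cord base excess outcome has the wrong sign, and the Statistical analysis section conflicts with Table 1 on number of agents, five unlisted outcomes and one respiratory definition

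*Protocol article*

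**What the plan says.** Under Exposure and outcomes, the protocol article gives Table 1 its status: "We have prespecified a number of secondary outcomes to assess the safety of home cervical ripening", with the list in that table. Among the baby safety outcomes, "Arterial cord blood pH <7.1" is followed directly by "Arterial cord base excess >12 mmol/L". Among the effectiveness outcomes stands "More than one cervical ripening agent used".

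The Statistical analysis section returns to the secondary outcomes. For the mothers it says "we will include hyperstimulation, ≥1 induction agent, oxytocin use for induction or augmentation", and the sentence ends with "haemorrhage, uterine rupture, pulmonary embolus and cardiorespiratory arrest". For the babies it names, among others, respiratory support, birth trauma and therapeutic hypothermia. The same section makes no formal adjustment for multiple comparisons and promises a caveat on type 1 error instead.

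The setting of the comparison matters here: "our primary comparison will be home dinoprostone versus in-hospital dinoprostone", with the comparator women drawn from units that do not offer home ripening.

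**The concern.** Three things look wrong.

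- **Direction of the base excess rule.** The item sits beside a low-pH item in a safety list, so it is evidently meant to mark acidosis. As printed it points the other way.
- **Number of agents.** The two sections give different thresholds for the same outcome, and one of them is met by everybody.
- **Two lists.** The article calls one list prespecified, then commits elsewhere to outcomes that the list does not contain.

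The data come from electronic maternity and neonatal records (Data sources), so each outcome must eventually become a rule applied to a field. Following the printed text would make the acidosis outcome uninformative wherever base excess is stored with its sign. If some sites stored a signed base excess and others a positive base deficit, one rule would mean different things at different sites. The primary comparison is between units, so such a difference would not cancel out. The agent outcome would have no variation to analyse. With many secondary outcomes and no multiplicity adjustment, the reader also needs to know which single list was fixed in advance.

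**Working it through.** **1. Base excess.** The inputs are the two adjacent Table 1 items. Acidosis lowers pH and makes base excess negative; a base deficit of 12 mmol/L is a base excess of -12 mmol/L.

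| Baby | pH below 7.1 | Base excess above +12 (as printed) | Base excess below -12 (base deficit above 12) |
|---|---|---|---|
| Marked metabolic acidosis | met | not met | met |
| Marked alkalosis | not met | met | not met |

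On a signed scale the printed rule runs opposite to its companion. If a field stores the magnitude of the deficit as a positive number, a threshold of more than 12 selects the intended babies. The article does not say which form the sites use, so no event rate can be attached to the error.

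**2. Number of agents.** In the primary comparison every woman in both groups receives dinoprostone, so the proportion with at least one agent is p = 1 in each.

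- Variance of the indicator: p(1 - p) = 1 × 0 = 0.
- With the planned 1920 evaluable women per arm, the counts are 1920 of 1920 against 1920 of 1920. The odds are 1920/0 in each group, so no odds ratio exists.
- Under Table 1's wording the outcome varies. The article gives no rate. Assuming 20% to 40%, the variance is 0.2 × 0.8 = 0.16 to 0.4 × 0.6 = 0.24, and the outcome can be analysed.

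**3. Comparison of the lists.** Table 1 has 19 baby and 8 maternal safety items, 27 in all. The Statistical analysis section names 16 safety outcomes. Matched item by item:

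| Status | Count | Items |
|---|---|---|
| In both | 10 | birth outside hospital, hyperstimulation, intensive care, high dependency care, haemorrhage, meconium aspiration, neonatal infection, cord prolapse, grade 2/3 encephalopathy, neonatal death |
| Statistical analysis only | 5 | uterine rupture; pulmonary embolus; cardiorespiratory arrest; neonatal birth trauma; therapeutic hypothermia |
| Defined differently | 1 | respiratory support against mechanical ventilation |

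That gives 10 + 5 + 1 = 16. Cord prolapse is common to both lists but is classed as maternal in Table 1 and neonatal in the text. Of the 27 Table 1 safety items, 27 - 10 = 17 are not named in the text.

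**4. Effect on the main design.** The stated sample size reproduces and uses none of these definitions. With 6% in both arms, a 4% margin, one-sided 2.5% and 90% power:

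- n = (1.960 + 1.282)² × 2 × 0.06 × 0.94 / 0.04² ≈ 741 per arm.
- The design effect is 1 + (160 - 1) × 0.01 = 2.59, and 741 × 2.59 = 1919, against the stated 12 × 160 = 1920.
- 1920 × 2 / 0.5 / 0.9 = 8533, as stated.

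**The case against.** The best defence is that these are slips in a condensed article. A clinician reading the base excess item beside the pH item will understand base deficit. Table 1 is named as the prespecified list and defines the agent outcome properly, so the looser wording in the Statistical analysis section can be settled by reading Table 1. Full specification is left to an analysis plan agreed by the Steering Committee, which is not shown here.

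Much of this stands, and it rules out several stronger readings that a reader might infer:

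- **That the acidosis outcome will be near 0% in both arms.** This needs signed storage and literal coding, and the article states neither.
- **That two Table 1 outcomes are badly defined.** Only the base excess item is; the agent item in Table 1 is usable.
- **That every woman in the whole data cohort has at least one agent.** The cohort is all inductions from 37 weeks, and the article does not say that each involved a ripening agent. The 100% holds for the primary dinoprostone comparison.
- **That a constant agent outcome would pass as evidence of no difference.** It could not be estimated at all, and that would be noticed.
- **That six outcomes are new.** Five are. Respiratory support is a different definition of an item that Table 1 covers as mechanical ventilation.
- **That stillbirth, seizures and intracranial haemorrhage have been dropped.** The text leaves 17 Table 1 safety items unnamed, including Apgar scores and cord pH. It is partly illustrative and is not a replacement list, so these omissions are not an error.
- **That selective reporting is intended or likely.** Nothing in the article shows this.

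The defence does not cover the rest. Condensing can shorten a list, but it does not explain outcomes that the article's own prespecified table lacks. An obvious intended meaning does not make the printed threshold correct.

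**Conclusion.** The point holds as a correction to secondary outcomes. One Table 1 definition, cord base excess, is wrong in direction on a signed scale. One outcome, number of agents, is stated in two contradictory ways, and one of the two has zero variance in the primary comparison. Five outcomes are committed to without being in the prespecified table, and one respiratory outcome has two definitions.

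The base excess conclusion rests on the ordinary meaning of base excess and on the adjacent pH item; how far the results would be affected depends on how sites store the value, which is not stated. The agent conclusion rests on both groups of the primary comparison receiving dinoprostone. The comparison of the lists rests on the article's text alone. The primary outcome, its analysis and the sample size of 8533 are not affected.

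**What to change.** - **Table 1, base excess:** write base deficit above 12 mmol/L (base excess below -12 mmol/L). Check how each site's field records the sign, and convert to one convention before applying the threshold.
- **Statistical analysis, agents:** replace at least one induction agent with Table 1's more than one cervical ripening agent.
- **One outcome list, settled before analysis:** either add the five outcomes to Table 1, marked as added, or remove them from the Statistical analysis section. Choose one of mechanical ventilation and respiratory support, and use it in both places. Put cord prolapse under one heading.

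The first two changes are textual, plus a check of field conventions. Reconciling the list is also a text change if the records already hold the fields. Any of the five outcomes that is kept without an existing field would need one set up at the sites, so the decision should be taken before extraction rules are written.
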